## Abstract

**Background:**

Minimal interventional procedures are frequently applied in patients with mechanical low back pain which is defined as pain presumably resulting from single sources: facet, disc, sacroiliac joint or a combination of these. Usually, these minimal interventional procedures are an integral part of a multidisciplinary pain programme. A recent systematic review issued by the Dutch Health Insurance Council showed that the effectiveness of these procedures for the total group of patients with chronic low back pain is yet unclear and cost-effectiveness unknown. The aim of the study is to evaluate whether a multidisciplinary pain programme with minimal interventional procedures is cost-effective compared to the multidisciplinary pain programme alone for patients with chronic mechanical low back pain who did not respond to conservative primary care and were referred to a pain clinic.

**Methods:**

All patients with chronic low back pain who are referred to one of the 13 participating pain clinics will be asked to participate in an observational study. Patients with a suspected diagnosis of facet, disc or sacroiliac joint problems will receive a diagnostic block to confirm this diagnosis. If confirmed, they will be asked to participate in a Randomized Controlled Trial (RCT). For each single source a separate RCT will be conducted. Patients with a combination of facet, disc or sacroiliac joint problems will be invited for participation in a RCT as well. An economic evaluation from a societal perspective will be performed alongside these four RCTs. Patients will complete questionnaires at baseline, 3 and 6 weeks, 3, 6, 9 and 12 months after start of the treatment. Costs will be collected using self-completed cost questionnaires.

**Discussion:**

No trials are yet available which have evaluated the cost-effectiveness of minimal interventional procedures in patients with chronic mechanical low back pain, which emphasizes the importance of this study.

**Trial registration number:**

National Trial Register: NTR3531

## Background

Non-specific low back pain is a widespread problem with major social and economical consequences [1,2]. Non-specific low back pain contains 85 – 90% of the low back pain diagnoses and is defined as low back pain not attributable to a recognisable, known specific pathology (e.g. infection, tumour, osteoporosis or fracture) [3-5]. The majority of the patients with low back pain are successfully treated in primary care, approximately 10 – 15% will develop chronic (more than three months) symptoms. In The Netherlands, costs of low back pain were estimated at €3.5 billion in 2007 [6]. Patients developing chronic symptoms are responsible for the majority of these healthcare and socio-economic costs [6]. Additionally, based on demographic developments, it is expected that the number of people with back problems will increase in the coming years [7,8]. Because of the enormous costs of this growing problem, effective interventions aimed at prevention and treatment of chronic low back pain are necessary.

In lower back pain, 80 – 90% is of mechanical origin [9,10]. Mechanical back pain implies that the source of the pain is in the spine or its supporting structures [9]. There is consensus among anaesthesiologists, that minimal interventional procedures are effective for patients with pain presumably resulting from single sources: facet, disc, sacroiliac (SI) joint or a combination of these (defined as mechanical low back pain) [11]. This is at odds with recently performed systematic reviews and multidisciplinary international clinical guidelines. These concluded that there is no strong evidence that supports the effectiveness of minimal interventional procedures in patients with chronic low back pain [12-17]. Most likely due to a lack of Randomised Controlled Trials (RCTs) with a low risk of bias and adequate sample size [12,18]. A recent systematic review issued by the Dutch Health Insurance Council (CVZ) showed that the effectiveness of minimal interventional procedures for the total group of patients with chronic low back pain is unclear and the cost-effectiveness unknown [19]. Based on this lack of evidence, CVZ advised the Ministry of Health in The Netherlands not to reimburse minimal interventional procedures for patient with chronic low back pain within the Dutch public health insurance system. The anaesthesiologists standpoint is that they merely treat a subgroup of patients: patients with mechanical low back pain, for which they argue that minimal interventional procedure would be effective [11].

### Aim

The aim of this project will be to provide a valid, reliable and precise answer to the question whether minimal interventional procedures supplementary to a multidisciplinary pain programme for patients with chronic mechanical low back pain who are referred to a pain clinic are more effective and cost-effective compared with the multidisciplinary pain programme alone.

## Methods

### Study design

An observational study and four RCTs with a full economic evaluation will be performed. The observational data will inform about the proportion of patients with a positive or negative diagnostic test for facet pain, disc pain, SI-joint pain and a combination of these, and the clinical outcomes of patients with a negative diagnostic test. Patients diagnosed with facet, disc, SI-joint or combination pain, by means of a diagnostic block will be asked to take part of one of the four RCTs. The observational study will monitor patients who do not want to, or are not eligible to participate in the RCTs. Figure 1 provides an overview of the study design and patient flow.

**Figure 1 F1:**
[figure not shown]
Trial design and patient flow.

### Ethical approval

In June 2012, the study was approved by the Medical Ethics Committee of the Erasmus Medical Centre in Rotterdam (registration number MEC-2012-079) and the study protocol was registered at the Dutch Trial Register (number NTR3531). Written informed consent will be obtained before entering the study.

### Study population

In this study all patients aged between 18 and 70 years, referred to a pain clinic with suspected chronic mechanical low back pain and without improvement of symptoms after conservative treatment will be invited to participate in the observational study. Further inclusion criteria for the RCTs are: a) a 50% or more reduction in perceived pain at 30 minutes after a diagnostic block; or b) the provocative discography must be positive. According to the International Association for the Study of Pain (IASP) and the International Spinal Injection Society (ISIS), a provocative discography is positive when the familiar pain at the target level is provoked with a pain score of 7 out of 10, and two painless adjacent control discs are present [20].

Exclusion criteria are pregnancy; inability to complete the questionnaires; anticoagulant drug therapy and/or coagulopathy; Body Mass Index higher than 35; involvement in a work related conflict; severe psychiatric or psychological problems. Patients will be asked to complete five questionnaires, three of which serve to indicate whether patients with psychiatric or psychological complaints need to be excluded. Distress, depression, anxiety, somatisation, pain acceptance and pain coping strategies will be assessed with the Four-Dimensional Symptoms Questionnaire (4DSQ) [21,22], the Chronic Pain Acceptance Questionnaire (CPAQ) [23,24], Hospital Anxiety Depression Scale (HADS) [25,26], Pain Coping Inventory (PCI) [27], and the Pain Cognition List (PCL) [28].

Only the 4DSQ (anxiety > 12; depression > 5; distress > 20; somatisation > 20), CPAQ (z-score > 2 in pain willingness) and PCL (z-score > 2 in catastrophizing and limitations) will be used for exclusion from the RCTs. Patients will be excluded if they score above the predefined thresh-hold in any of the questionnaires.

Patients are recruited in the pain-treatment clinics of the participating hospitals. General practitioners and medical specialists who referred patients to the pain clinics will be informed about participation of their patients in the study. The anaesthesiologists identify and inform potential participants from among their clinic’s patients. If a patient meets the eligibility criteria and agree to participate in the trial, the patient will be asked to sign an informed consent form.

### Setting

Anaesthesiologists at the participating clinics will conduct the diagnostic tests and the minimal interventional procedures. Every participating pain clinic has a referral agreement with three or four physiotherapy practices in their region. These will provide a standardized exercise programme. The psychological interventions, if necessary, will take place in a usual care setting.

### Multidisciplinary pain programme

Each patient will receive the exercise programme and psychological help (if necessary). The patient in the intervention group will receive the Minimal Interventional Procedures as well. Together, this will form the multidisciplinary pain programme. The selection of eligible patients in the diagnostic phase by performing a test block, as well as the exercise programme (which we standardized for the study) and the minimal interventional procedures are usual care at Dutch pain clinics, as described in the current guideline anaesthesiological pain control [11,29].

#### Exercise programme

All participants of the trials will receive a standardized exercise programme based on the guideline low back pain of the Royal Dutch Society for Physical Therapy [30]. The programme consists of graded exercise therapy with focus on quality of movement (local stabilizers) and behavioural aspects, generally based on the programme of Lindström et al. [31,32]. As the application of these guidelines can vary between physiotherapists, a standardized version of the original programme is developed for this study in cooperation with Sports Medical Center Papendal. All physiotherapists participating in the study have ample experience with exercise therapy with focus on behavioural aspects. Furthermore, all physiotherapists will follow a three to four hour introduction session prior to the study. The main aim of the exercise programme is restoring physical function. An individually graded exercise programme will be offered to the patient explaining that it is safe to move while increasing the level of activity. During the exercise programme the patient has an active role and the physical therapist acts as a coach and supervisor, using a hands-off approach. The entire programme will be spread over three months with a treatment range between eight to twelve hours (one to two sessions per week).

#### Psychological support

If necessary, the anaesthesiologist or physiotherapist can refer the patient to the psychologist. The patients will receive usual care.

#### Minimal interventional procedures

Supplementary to the exercise programme, and possibly a psychological support, the intervention group will receive minimal interventional procedures. This will take place according to a pre-specified approach, based on the current guideline anaesthesiological pain control [11]:

1. Patients with facet joint pain will receive radiofrequency lesion of the first ramus dorsalis at Lumbar vertebrae (L)3, L4, L5 and S1.

2. Patients with intervertebral disc pain will receive Intradiscal Electrothermal Therap (IDET) or Biacuplasty of the involved disc.

3. Patients with SI- joint pain will receive the Cooled radiofrequency, radiofrequency lesion pallisade technique or Simplicity III probe technique of the ramus dorsalis at L4, L5, S1, S2 and S3.

4. Patients with a combination of the single entities will be divided, after the clinical diagnosis, to a group who receives minimal interventional treatments (i.e. a combination of the interventions mentioned under 1, 2 and 3).

In both treatment groups, the patients are asked to refrain from any co-interventions during the intervention period. However, co-interventions after the initial intervention period will be monitored and evaluated. If patients in the non-interventional study group have not improved or recovered after three months, they will not receive interventional procedures but will return to the General Practitioner or medical specialist that had referred them to the pain clinic.

### Baseline measurement & outcomes

The core set of primary outcomes recommended for low back pain research will be used [33]. All web-based questionnaires will be assessed at baseline, three, six, nine and twelve months after the start of the treatment. Quality Adjusted Life Years (QALY), pain intensity and global perceived recovery will be assessed at three and six weeks as well.

#### Baseline measurement

The baseline questionnaire includes socio-demographic characteristics (age, gender, marital status etc.), the complaint history, all primary and secondary outcomes and patient expectation. Patient expectation will be assessed with the 10-point scale Credibility/Expectancy Questionnaire (CEQ) [34,35].

#### Primary outcomes

There are three primary outcomes: pain intensity, global perceived recovery and functional status.

Pain intensity over the previous week will be measured on an 11-point Numerical Rating Scale (NRS) (0 = no pain to 10 = worst imaginable pain) [36]. Among chronic low back pain patients, the NRS is the most appropriate, valid and reliable measurement [37,38].

Global perceived recovery will be measured by self-assessment on a 7-point NRS ranging from ‘completely recovered’ to ‘worse than ever’, as for example described by Kamper et al. [39]. This instrument is often used in low back pain research [35,40].

Functional status will be measured according to the Dutch translation of the Oswestry Disability Index (ODI-NL) [41]. This index consists of ten questions addressing common daily activities. Each question has six answer options, scored 0-5, from which 0 is related to ‘no restriction in daily activities’ to 5 ‘the most restrictions in daily activities’. The ODI has shown to be valid and reliable in chronic pain experience studies and is widely used in low back pain research [42,43].

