**Primary outcomes**							
Pain Intensity (NRS)	x	x	x	x	x	x	x
Global perceived recovery (NRS)		x	x	x	x	x	x
Functional Status (ODI)	x			x	x	x	x

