### Statistical analysis

Baseline data will be presented comparing the two treatment groups. Intention-to-treat analysis will be conducted for each follow-up moment. Missing data will be imputed with multiple imputation techniques [56,57]. The 95%-confidence intervals will be calculated for the difference of percentages (Chi-square distribution) and means (T-distribution) for dichotomous and continuous outcome variables, respectively. In case of unequal distributions of prognostic factors, multivariate analysis techniques will be used to correct for these between-group differences in prognosis. Multilevel analyses will be performed, with patient, pain clinic, and time of measurement as levels. The threshold of statistical significance is set at *p* < 0.05. Characteristics of patients with missing follow-up data will be compared to those with complete data to identify possible selective drop-out.

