### Economic evaluation from a societal perspective

The economic evaluation will be performed according to the intention-to-treat principle and from a societal perspective. Costs of the minimal interventional procedures, physiotherapy, other health care utilization, patient and family costs, and costs of production losses will be measured and valued. Data are collected through self-completed cost questionnaires.

Missing costs and effect data will be imputed using multiple imputation according to the Multivariate Imputation by Chained Equations procedure corrected and accelerated (Bca) bootstrapping with 5000 replications will be used to estimate confidence intervals around differences in total costs between treatment groups [58,59].

A cost-effectiveness and a cost-utility analysis will be performed. Incremental cost-effectiveness ratios will be calculated by dividing the difference in mean costs by the difference in the mean effects of the two treatment groups. Using a primary clinical effect measures of the trial, for instance pain intensity. Cost-utility will be based on the EQ-5D and expressed in costs per QALY. Uncertainty surrounding incremental cost-effectiveness and cost-utility ratios will be estimated using bootstrapping techniques and graphically presented in cost-effectiveness and cost utility planes. Cost-effectiveness acceptability curves and net monetary benefit will also be estimated. Sensitivity analyses on the most important cost drivers will be performed in order to assess the robustness of the results.

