Based on clinical experience we hypothesize that for patients with chronic mechanical low back pain, a multidisciplinary pain programme with minimal interventional procedures will be more effective than a programme without these procedures. The main expected effect is short-term pain reduction, but it is likely that this will be associated with improved functioning and quality of life. The costs of minimal interventional procedures are approximately (depending on the treating hospital and the health insurance company) between €2500,- and €3500,- per treatment [65]. We expect that the average costs of patients who receive minimal interventional procedures are higher than those of patients in the control group. However, if clinical outcomes are better minimal interventional procedures may be cost-effective if the incremental costs are worthwhile. Also, improved clinical outcomes and more rapid recovery might result in less additional health care consumption and lower costs of work absenteeism and consequently in lower additional costs.

This study will provide more knowledge on the treatment of chronic mechanical low back pain. Furthermore, results of this project will be included in future updates of the clinical guidelines of low back pain. The Dutch Association of Anaesthesiology supports this project and will use the results in a future update of their clinical guidelines. Finally, the results of this study will inform governmental policy regarding reimbursement of minimal interventional procedures for chronic mechanical low back pain. The results of the trials are expected to be available at the end of 2015.

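### Each trial has three unranked primary outcomes analysed at every follow-up at p < 0.05, with no primary time point or success rule, although it is sized for one pain comparison

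*Protocol article*

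**What the plan says.** Under Primary outcomes: "There are three primary outcomes: pain intensity, global perceived recovery and functional status". No order of importance is given.

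Under Baseline measurement & outcomes: "All web-based questionnaires will be assessed at baseline, three, six, nine and twelve months after the start of the treatment", and "pain intensity and global perceived recovery will be assessed at three and six weeks as well". Table 1 agrees: after baseline, pain and global recovery are each measured six times and the ODI four times.

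Under Statistical analysis: "Intention-to-treat analysis will be conducted for each follow-up moment", with 95% confidence intervals for differences in percentages and means. The same section plans multilevel analyses with patient, clinic and time as levels. It closes with one general threshold: "The threshold of statistical significance is set at" p < 0.05.

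Under Sample size, each trial is sized on pain alone: difference 2 points, SD 4, alpha 0.05, power 0.9, correlation 0.5 for repeated measurements. The result is 85 per group, with no time point named.

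The only hint of a time frame is a hypothesis in the Discussion: "The main expected effect is short-term pain reduction". For the clinical cost-effectiveness ratio, the economic section says "Using a primary clinical effect measures of the trial, for instance pain intensity".

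**The concern.** The sample size assumes one confirmatory test per trial. The outcome and analysis sections provide many candidates for that test and do not say which one decides. Pain might differ at 3 weeks and not at 12 months, or pain might improve while the ODI does not. Either pattern could be reported as a positive or a negative trial, and nothing in the text settles which.

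This matters more here for two reasons. All outcomes are self-reported by patients who know their allocation. The results are also intended to inform guidelines and reimbursement. The open choice of effect measure for the clinical cost-effectiveness ratio carries the same ambiguity into the economic analysis.

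**Working it through.** **1. The plan's own figure.** With a difference of 2, SD 4, two-sided alpha 0.05 and power 0.90:

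n per group = 2 × (1.960 + 1.282)² × 4² / 2² = 84.06, rounded up to 85.

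The stated 85 is reproduced (a one-sided test would need 69). The stated correlation of 0.5 does not change this for a change score, because its SD is 4 × √(2 × (1 − 0.5)) = 4. Averaging m follow-ups at correlation 0.5 multiplies the variance by (1 + 0.5(m − 1))/m:
- m = 4: 84.06 × 0.625 = 52.5, so 53 per group.
- m = 6: 84.06 × 0.583 = 49.03, so 50 per group.

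The 85 therefore corresponds to one outcome at one time.

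**2. Number of comparisons (Table 1).** Pain 6 + global recovery 6 + ODI 4 = 16 per trial.

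**3. Chance of at least one false positive per trial, if any significant primary result counts as success.** For independent tests this is 1 − 0.95^k: 0.560 for k = 16 and 0.143 for k = 3. For correlated tests, 400,000 null draws were simulated from a multivariate normal. Two comparisons are correlated by the over-time value if their visits differ, times the between-outcome value if their outcomes differ. The article gives only the 0.5 for repeated measurements; every other correlation is an assumption.

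| Correlation over time / between outcomes | Any of 16 | Any of 3 |
|---|---|---|
| Independent | 0.560 | 0.143 |
| 0.3 / 0.3 | 0.508 | 0.136 |
| 0.5 / 0.5 | 0.425 | 0.125 |
| 0.5 / 0.7 | 0.381 | 0.109 |
| 0.7 / 0.5 | 0.350 | 0.126 |
| 0.7 / 0.7 | 0.308 | 0.109 |
| 0.8 / 0.8 | 0.242 | 0.099 |
| 0.9 / 0.9 | 0.167 | 0.083 |

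The last column covers three outcomes at one time. It also approximates a multilevel model that yields one test per outcome.

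**4. Power for pain under the two remedies.** Power ≈ Φ(0.5 × √(n/2) − z), where 0.5 = 2/4. Completers per arm are 102 × 0.8 = 81.6, about 82.
- One primary test, z = 1.960: 0.903 with 85 per arm; Φ(3.202 − 1.960) = 0.893 with 82.
- Holm, first step at 0.05/3 = 0.0167, z = 2.394: Φ(3.260 − 2.394) = 0.807 with 85; Φ(3.202 − 2.394) = 0.790 with 82.

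To restore 90% power for pain at alpha 0.0167 would take 109 per group before withdrawal. No effect size or SD is given for recovery or the ODI, so their power cannot be computed.

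**The case against.** Several points on the other side have force.

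- **No success rule is stated.** A reader might infer that the plan lets any one of 16 results make a trial positive. It does not say so. It sets a threshold and is silent on what makes a trial positive, so the error rates above depend on that any-result reading. A rule requiring all three outcomes at one fixed time would hold 5% without adjustment, but no such rule is stated either.
- **A multilevel analysis is planned.** It could give a single treatment effect per outcome, hence 3 tests and not 16. The text does not say that it replaces the per-visit comparisons, and it names no contrast. On this reading the excess shrinks to 8% to 14% but does not disappear.
- **The per-visit analysis is partly estimation.** Confidence intervals are specified, and the threshold is one general sentence. This softens the count of 16 tests but still leaves open which interval answers the trial's question.
- **Detail may sit in an unseen analysis plan.** Testing order and adjustment method are commonly left there, and their absence is not the point. The article itself fixes three equal primaries, analysis at each visit and one threshold, and these do not match its one-comparison sample size.
- **The three outcomes are a recommended core set.** That justifies measuring all three. It does not say how a mixed result is to be read.
- **Reimbursement also rests on the economic analysis.** This is true: that analysis uses bootstrapping, acceptability curves and net monetary benefit, and its QALY measure is already fixed on the EQ-5D. Only the clinical effect measure is open.

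**Conclusion.** The point stands in this form: three unranked primary outcomes, analysed at each follow-up with one p < 0.05 threshold, have no primary time point or success rule, while the sample size assumes one pain comparison at 0.05.

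Under an any-result reading, the per-trial false-positive chance is about 17% to 51% over 16 comparisons, and 31% to 43% at correlations of 0.5 to 0.7. With one test per outcome it is about 8% to 14%. The 56% for independent tests is a reference figure, since repeated measures on the same patients are correlated. All these figures rest on assumed correlations and on a success rule that the article neither states nor excludes. They show what the present wording permits and are not an established error rate for the trial.

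A reader might also infer that error must be controlled across the four trials. The article sets them up as separate trials in separately diagnosed groups, each with its own comparison, so the issue stays within each trial.

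**What to change.** Before data are seen, name one primary comparison for each trial: pain NRS, the outcome used for the sample size, at one stated time, estimated from the multilevel model and tested at two-sided 0.05. Three months is a reasonable example, because it is the end of the exercise programme and fits the short-term hypothesis. The article does not dictate it, and another time fixed in advance would also cure the problem. Report global recovery, the ODI and the other visits as secondary estimates with 95% confidence intervals. This keeps 85 per group.

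If the three core outcomes are to remain primary, test them at that single time with Holm's procedure and restate the power for pain: about 79% at the first step with 82 completers per arm, about 81% with 85.

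Name the clinical effect measure for the cost-effectiveness ratio in place of an example. The QALY measure needs no change.

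The cost is about one paragraph in the protocol or analysis plan and a matching registry update. The downside is that only one result per trial, or Holm-adjusted results with lower power, carries the confirmatory claim.
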